#### **8.4.3 Safety Analysis**

The set of subjects included in the safety analysis is those subjects who receive at least one dose of trial drug and who have follow-up safety data.

### **8.5 Description of Statistical Analyses**

#### **8.5.1 General Considerations**

All statistical tests will be performed at the 0.05 significance level. 95% confidence intervals will be calculated whenever appropriate.

Only available data will be considered for analysis. Subjects who discontinue the study prematurely will be considered as missing data and will be dropped from the statistical analysis.

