### **5.3.5 Criteria for Subject Withdrawal**

Subjects are free to discontinue the trial at any time without giving their reasons.

A subject must be withdrawn in the event of any of the following:

1. Withdrawal of the subject's consent.
2. Occurrence of an exclusion criterion which is clinically relevant and affects the subject's safety, if discontinuation is considered necessary by the Investigator.
3. Intolerance to Concor® treatment.
4. Occurrence of unexpected adverse events that are unacceptable in nature, severity and/or duration, or the frequency of known unacceptable adverse events is higher than expected.

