## **7.1 Trial procedures and assessments**

### **7.1 Trial schedule and assessment contents**

The trial procedure and assessment contents are as follows:

1. Visit 1 -Week -1 (1 +3 day): this visit entails the following:

Before any procedures that are related to the trial is undertaken, informed consent of the patient should be obtained. Thereafter, basic information of the patient will be obtained and patients are screened for eligibility based on the inclusion and exclusion criteria.

- ①. Record birth date, gender, height, weight, waist circumstance, current medical condition and past medical history, including concomitant therapies.
- ②. Perform physical examinations, including vital signs (blood pressure, heart rate).
- ③. Blood tests: full blood count (white blood cells, neutrophils, red blood cells, hemoglobin and platelets), liver function (ALT, AST), renal function (Bun, Cr), fasting blood glucose and blood lipids (TC, TG, LDL-C and HDL-C).
- ④. 12-Lead ECG and echocardiography

- ⑤. Sepical tests: central blood pressure, BRS, BPV, HRV, Holter and 24 h-ABPM
2. Visit 2-Week 2 (14+3 days): this visit entails the following:
- ①. Perform physical examinations, including vital signs (blood pressure, heart rate), 12-Lead ECG.
  - ②. If the RHR is lower than 65 bpm, test BRS, BPV, HRV. Remain the treatment for an extended 2-week, then go for Last visit.
  - ③. Record AE and concomitant therapies.
3. Visit 3-Week 4 (28 +3 days): this visit entails the following:
- ①. Perform physical examinations, including vital signs (blood pressure, heart rate), 12-Lead ECG.
  - ②. If the RHR is lower than 65 bpm, test BRS, BPV, HRV. Remain the treatment for an extended 2-week, then go for Last visit.
  - ③. If the RHR is still higher than 65 bpm, adjust the dosage of bisoprolol or atenol according to blood pressure and heart rate. After 2 weeks, go for Visit 4.
  - ④. Record AE and concomitant therapies.
4. Visit 4-Week 6 (42+3 days): this visit entails the following:
- ①. Perform physical examinations, including vital signs (blood pressure, heart rate), 12-Lead ECG.
  - ②. If the RHR is lower than 65 bpm, test BRS, BPV, HRV. Remain the treatment for an extended 2-week, then go for Last visit.
  - ③. If the RHR is still higher than 65 bpm, directly go for Last visit.
  - ④. Record AE and concomitant therapies.
5. Last Visit- End of extended treatment:
- ①. Perform physical examinations, including vital signs (blood pressure, heart rate), 12-Lead ECG.

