### **8.3 Endpoints**

#### **8.3.1 Primary Endpoint(s)**

The primary endpoint is BRS and central blood pressure at Last visit.

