### **8.4 Analysis Sets**

#### **8.4.1 PP and ITT Analysis**

The main analysis set will be defined as all subjects who receive at least one dose of any investigational medicinal product, i.e., the Intention-to-Treat (ITT) population. This population will be used for all efficacy evaluations. A secondary analysis set, the Per Protocol

(PP) set, will also be defined, which will exclude all subjects found to have a major protocol deviation\*.

\*Deviation from the protocol will be determined by medical check.

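### Section 8.5.1 drops every patient who discontinues early, contradicting the ITT set of 8.4.1 and leaving a completers-only main analysis open to selection bias of unknown size and direction

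*Protocol*

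**What the plan says.** Protocol section 8.4.1 defines the main analysis set as "all subjects who receive at least one dose of any investigational medicinal product, i.e., the Intention-to-Treat (ITT) population", and adds: "This population will be used for all efficacy evaluations". A per-protocol set, which removes major deviators, is secondary.

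Section 8.5.1, which sets general rules for the statistical analyses, says first "Only available data will be considered for analysis" and then "Subjects who discontinue the study prematurely will be considered as missing data and will be dropped from the statistical analysis". It makes no exception for the ITT set, the primary endpoint or safety.

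Four other places bear on this:

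- Section 8.3.1: "The primary endpoint is BRS and central blood pressure at Last visit".
- Section 7.1 schedules central pressure only at Visit 1 and the Last visit. At Visits 2 to 4 the rule is "If the RHR is lower than 65 bpm, test BRS, BPV, HRV". Heart rate and peripheral blood pressure are taken at every visit.
- Section 5.3.5 makes withdrawal mandatory for several reasons, including unacceptable adverse events and "Intolerance to Concor® treatment".
- Section 8.4.3 keeps in the safety analysis every dosed patient who has follow-up safety data.

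**The concern.** The two efficacy rules give different answers for the same patient. If 8.5.1 is applied, the result reported as ITT describes only those who finished. If 8.4.1 is applied, 8.5.1 is breached. The protocol does not say which rule prevails, so the choice could be made after the data are seen. An analysis plan could not settle this by adding detail, because the protocol itself fixes both rules.

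At stake is the randomised comparison on the primary endpoint. Patients leave for tolerability, adverse events or consent. If those reasons differ between the drugs and relate to BRS or central pressure, the completers in the two arms are no longer comparable. Read literally, the sentence also removes patients withdrawn for adverse events from the safety summary, against 8.4.3.

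**Working it through.** **Step 1: one patient under each rule.** Take a dosed patient who reaches a resting heart rate below 65 bpm at Visit 2, has BRS tested, and stops in week 3.

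| Rule | Treatment of this patient |
|---|---|
| 8.4.1 | In the ITT set, so in all efficacy evaluations |
| 8.5.1, available-data sentence | Visit 2 BRS, heart rate and peripheral pressure exist and could be used |
| 8.5.1, dropping sentence | Removed altogether |
| 8.4.3 | In the safety set if follow-up safety data exist |

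The dropping sentence conflicts with 8.4.1, with 8.4.3 on a literal reading, and sits badly with the sentence before it.

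**Step 2: who is selected out.** Under section 7.1, patients still above 65 bpm after the last dose step go straight to the Last visit. They complete the study. Section 5.3.5 contains no lack-of-efficacy criterion. Selection therefore acts through intolerance, adverse events, a clinically relevant exclusion criterion or consent.

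**Step 3: the plan's own figure.** Section 8.1 gives 110 patients with no effect size, SD, power or dropout rate, so there is no calculation to reproduce. The 1:1 ratio in 8.2 gives 110 / 2 = 55 per arm. (Section 5.1 also shows 96 per arm, a separate inconsistency; 55 is used here.)

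**Step 4: illustrative bias with no true drug difference.** Dropout rates d and the correlation rho between dropout propensity and outcome are assumptions. Outcomes are in SD units and the test is two-sided at 0.05 (8.5.1 gives the level but not the sidedness).

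- Shift in the completers' mean, per arm: rho × k(d), with k(d) = φ(z_d) / (1 − d), where z_d is the normal quantile at d.
- k(0.05) = 0.1031 / 0.95 = 0.109; k(0.15) = 0.2332 / 0.85 = 0.274; k(0.20) = 0.2800 / 0.80 = 0.350.
- Bias b = rho × [k(d_A) − k(d_B)].
- SE = √(1/n_A + 1/n_B), with completers n = 55 × (1 − d): 52.25, 46.75 and 44 at 5%, 15% and 20%.
- Type I error = 1 − Φ(1.96 − b/SE) + Φ(−1.96 − b/SE).

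| Dropout | rho | Bias (SD) | SE | Type I error |
|---|---|---|---|---|
| Equal in both arms, same rho | any | 0 | – | 5.0% |
| Any rates | 0 | 0 | – | 5.0% |
| 15% vs 5% | 0.3 | 0.05 | 0.201 | 5.7% |
| 15% vs 5% | 0.5 | 0.08 | 0.201 | 7.0% |
| 20% vs 5% | 0.3 | 0.07 | 0.205 | 6.4% |
| 20% vs 5% | 0.5 | 0.12 | 0.205 | 9.1% |

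For example, at 20% versus 5% and rho 0.5: b = 0.5 × (0.350 − 0.109) = 0.121; b/SE = 0.121 / 0.2046 = 0.59. A simulation of the 20% versus 5% case gave 6.3% and 9.0%, in agreement.

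**Step 5: scale.** The difference detectable with 80% power is (1.960 + 0.842) × √(2/n). It is 0.53 SD with 55 per arm and 0.60 SD with 44 per arm (20% dropout in both). The illustrated bias is small beside these, but not negligible for the error rate.

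**The case against.** The strongest defence is that 8.5.1 only means a complete-case analysis within the ITT set. Early stoppers will usually have no Last-visit value, and central pressure is never measured between Visit 1 and the Last visit. For the primary endpoint, dropping the patient and dropping the missing value then nearly coincide. This stands in part: little primary-endpoint data is discarded beyond interim BRS, and most of the loss of information would occur under any method. It does not remove the conflict, because the sentence drops subjects rather than values. Even on the narrow reading, the main result is still a completers comparison under an ITT label.

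Three stronger readings are tempting, and the documents do not support them.

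- A reader might infer that poor heart-rate responders are selected out. Step 2 shows that they complete.
- A reader might infer from the Concor-only item that withdrawal must be higher on bisoprolol. The items on consent, exclusion criteria and adverse events cover both arms, and wording that names only Concor recurs elsewhere (the non-permitted medicines section and section 7.4.1.1), which may be carried-over text. Nothing in the protocol supports a 20% versus 5% split.
- A reader might infer that the result will favour one drug. If those withdrawn were the stronger pressure responders, the bias would reverse.

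The dosed-patient definition of ITT, as opposed to all randomised, is a common modification and a lesser point.

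**Conclusion.** The contradiction between 8.4.1 and 8.5.1 is certain from the text and must be corrected, because it decides who is in the primary analysis. Followed as written, 8.5.1 yields a completers-only comparison of Last-visit BRS and central pressure. That comparison is open to selection through tolerability, adverse events or consent.

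The amount of bias is not established. It ranges from zero, when dropout is equal and similarly outcome-related or unrelated to outcome, to about 0.12 SD with a type I error near 9% in the most unequal case shown. Those figures rest on assumed dropout rates and correlations, 55 patients per arm and a two-sided test. They show that the rule can matter, not that it will.

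**What to change.** 1. Delete the sentence in 8.5.1 that drops early discontinuers.
2. State in 8.4.1 that the main efficacy analysis includes all randomised patients, or at least all dosed patients as it now says, in the arm assigned.
3. Use all data these patients contributed, including interim BRS, heart rate and peripheral pressure.
4. Name in advance a method for missing Last-visit values that conditions on the Visit 1 value and interim data. A baseline-adjusted model with multiple imputation is one example; others would serve.
5. Keep the completers analysis as a sensitivity analysis only.
6. Optionally, seek the Last-visit tests from patients who stop treatment and agree. These tests are not already scheduled for them: the Last visit is tied to the end of extended treatment, and 5.3.5 withdraws subjects from the trial. This step needs a defined visit time and a few extra assessments.

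Steps 1 to 5 cost wording, some analysis work and an explicit missing-data assumption. Imputation will recover only part of the lost information, and patients who stop before Visit 2 have no interim data. The item in 5.3.5 that names only one of the two drugs should be reconciled separately.

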### ***Serious Adverse Event***

A serious adverse event (SAE) is any untoward medical occurrence that at any dose:

- Results in death.
- Is life-threatening.

NOTE: The term “life-threatening” in this definition refers to an event in which the subject is at risk of death at the time of the event; it does not refer to an event that hypothetically might cause death if it were more severe.

- Requires inpatient hospitalization or prolongation of existing hospitalization.
- Results in persistent or significant disability/incapacity.
- Is a congenital anomaly/birth defect.
- Is otherwise considered as medically important.

Important medical events that may not result in death, be life-threatening, or require hospitalization may be considered as SAEs when, based upon appropriate medical judgment, they may jeopardize the subject or may require medical or surgical intervention to prevent one of the outcomes listed in this definition. Examples of such events include allergic bronchospasm requiring intensive treatment in an emergency room or at home, blood dyscrasias or convulsions that do not result in inpatient hospitalization.

Relevant serious adverse events that need to be intensively monitored in this trial:

1. III Degree atrioventricular block;

2. Severe asthma attack;
3. Cardiac arrest
4. Acute pulmonary edema;
5. Worsening heart failure;
6. Shock.

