### **Events that Do Not Meet the Definition of an SAE**

Elective hospitalizations to simplify study treatment or study procedures are not considered an SAE. However, all events leading to unplanned hospitalizations or unplanned prolongation of an elective hospitalization must be documented and reported as SAEs.

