#### **7.4.1.3 Expedited Reporting of Serious Adverse Events**

As soon as the Investigator detects a serious adverse event, as defined above, associated with the study medication, he/she will report it within 24 hours (by e-mail, phone, or fax) to principal investigator [name].

The Investigator must promptly respond to any request for follow-up information or questions from the Sponsor. Serious adverse events occurring during the study must be monitored and followed up by the Investigator until stabilization or until the outcome is known, unless the subject is lost to follow-up. The Investigator will ensure any necessary additional therapeutic measures and follow-up procedures.

Reporting procedures and timelines for any new information on a previously reported serious adverse event (follow-up) are the same as for the original report.

Further to reporting serious adverse events to the Sponsor, the Investigator will comply with any applicable local pharmacovigilance requirements to report adverse reactions/events to national pharmacovigilance systems.

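### The rule that drops premature discontinuers (Section 8.5.1) does not exempt safety and contradicts the safety set (Section 8.4.3); two other safety clauses need minor rewording

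*Protocol*

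**What the plan says.** **Drop rule.** Section 8.5.1, which opens the description of the statistical analyses, says "Only available data will be considered for analysis" and then "Subjects who discontinue the study prematurely will be considered as missing data and will be dropped from the statistical analysis". It does not limit either sentence to efficacy.

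**Safety set.** Section 8.4.3 bases the safety analysis on "those subjects who receive at least one dose of trial drug and who have follow-up safety data". Section 8.3.2 makes the AEs recorded in the study the safety endpoint.

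**Withdrawal.** Section 5.3.5 lets subjects leave at any time without a reason. It makes withdrawal compulsory for, among other grounds, intolerance to Concor (item 3) and "Occurrence of unexpected adverse events that are unacceptable in nature, severity and/or duration" (item 4).

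**SAE reporting.** Under Section 7.4.1.1 an SAE "is any untoward medical occurrence that at any dose" meets one of the listed seriousness criteria; causality plays no part. Unplanned hospitalisations "must be documented and reported as SAEs". Section 7.4.1.2 requires a safety form for every SAE. The only deadline is in Section 7.4.1.3, for the investigator who "detects a serious adverse event, as defined above, associated with the study medication, he/she will report it within 24 hours". Timelines for follow-up information "are the same as for the original report".

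**The concern.** Comparing the safety of the two drugs is a stated objective, and AEs leading to discontinuation are among the most informative safety data in a short beta-blocker trial. A general analysis rule that drops every premature discontinuer, placed after the definitions of the analysis sets, can be read as overriding the safety set. An analyst who follows it would report AEs in completers only. A table of AEs leading to discontinuation would be empty by construction.

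Two other safety clauses raise smaller questions. The 24-hour SAE deadline carries a condition that the SAE definition does not. The compulsory intolerance criterion names only one of the two study drugs.

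**Working it through.** **1. Sections 8.4.3 and 8.5.1 side by side.** Take a patient who received at least one dose, had an AE recorded at a visit, and then left the trial.
- Section 8.4.3: dosed, with follow-up safety data, so included.
- Section 8.5.1: discontinued prematurely, so dropped.

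Both cannot be followed. The available-data sentence does not reconcile them, because the sentence after it removes the subject and not merely the missing values. Section 5.3.5, items 3 and 4, shows that such patients are expected.

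**2. Effect on AE incidence in one arm.** The protocol states no AE or discontinuation rate, so there is no figure to reproduce. Let n be the number in the arm's safety set, a the number with at least one AE, d the discontinuers with an AE, and e the discontinuers without one. Section 8.5.1 drops d + e.
- Before dropping: a/n.
- After dropping: (a − d)/(n − d − e).
- Change: [a(d + e) − nd] / [n(n − d − e)].

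Incidence falls when d/(d + e) exceeds a/n, and rises when it is smaller.

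Illustration: n = 110/2 = 55 (Section 8.1, and the 1:1 ratio in the first section numbered 8.2), taking all 55 to be in the safety set. The values of a, d and e are assumed.

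| a | d | e | Before | After |
|---|---|---|---|---|
| 10 | 6 | 0 | 10/55 = 18.2% | 4/49 = 8.2% |
| 10 | 1 | 0 | 10/55 = 18.2% | 9/54 = 16.7% |
| 10 | 1 | 5 | 10/55 = 18.2% | 9/49 = 18.4% |

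Check of the last row: (10 × 6 − 55 × 1)/(55 × 49) = 5/2695 = +0.2 points. The direction therefore depends on the mix of discontinuers. What does not depend on it is that d patients with AEs, and every AE that caused a discontinuation, leave the analysis.

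**3. SAE deadline.** The documentation, form, reporting and follow-up duties in Sections 7.4.1.1 to 7.4.1.3 cover SAEs generally but carry no time limit of their own, and the follow-up timeline only points back to the initial report. The single deadline, 24 hours, attaches to an SAE associated with study medication. If that is read causally, an SAE judged unrelated has no deadline. If it is read as association in time, as in the AE definition in Section 7.4.1.1, there is no gap.

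**4. Brand name.** Section 5.3.5 item 3, Section 6.3 (Non-permitted Medicines) and the causality sentence in Section 7.4.1.1 all say Concor, evidently meaning bisoprolol. Read literally, Section 6.3 would forbid atenolol in the atenolol arm, which cannot be intended. In Section 5.3.5, atenolol intolerance is reached through item 2 (beta-blocker intolerance is an exclusion criterion), at the investigator's discretion, or in some cases through item 4.

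**The case against.** The best defence is that Section 8.4.3 is the specific rule for safety and Section 8.5.1 a general one about missing data, suited to endpoints measured at the last visit. An AE already recorded is not missing, and a specific rule normally prevails. Many analysts would read it that way, so the harm is conditional on someone not doing so. That stands, and it makes this a clarification rather than a failed safety analysis. It does not remove the contradiction, because Section 8.5.1 does not say that it yields.

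A reader might go further in three ways that the protocol does not support.
- *That dropping discontinuers can only lower an arm's AE incidence, by at most 1/55 = 1.8 points per patient.* This holds only if every dropped patient had an AE and all 55 are in the safety set. The rule drops all premature discontinuers, and the last row of the table shows a rise. The safety set may also be smaller than 55, which would make the possible fall per patient larger.
- *That the 24-hour clause is an outright error.* It is narrower than the SAE definition on one reading and harmless on another. It applies equally to both arms, so it does not bias the comparison.
- *That naming only Concor makes withdrawal materially unequal between arms.* Literally, it is mandatory for one drug and largely discretionary for the other. But the same slip elsewhere points to a brand name left in place, intolerance is itself a clinical judgement, and any subject may leave at will. AEs are recorded in both arms under Section 7.4.1.2, and the further causality wording in Section 7.4.1.1 refers to the treatments generally.

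**Conclusion.** The contradiction between Sections 8.4.3 and 8.5.1 is real and should be corrected. Applied literally, Section 8.5.1 would take AEs that led to discontinuation out of the safety comparison. Neither the direction nor the size of the net change in AE incidence can be derived from the protocol; the percentages above rest on assumed counts and show only that either direction is possible. Section 5.1 prints 96 beside each arm, which does not agree with a total of 110, but the conclusion does not depend on the number per arm.

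The SAE deadline and the brand-name wording are minor. The first is an ambiguity about timing with no effect on the comparison. The second is a slip whose practical effect is probably small.

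**What to change.** **Main change, Section 8.5.1.** Add: *This rule does not apply to the safety analysis, which uses the set defined in Section 8.4.3; all AEs recorded up to discontinuation are included.* Leave Section 8.4.3 as it is.

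**Minor changes.**
- Section 7.4.1.3: require a 24-hour report of any SAE, in either arm and regardless of causality.
- Section 5.3.5 item 3, Section 6.3 (Non-permitted Medicines) and the causality sentence in Section 7.4.1.1: replace Concor with *the allocated study drug (bisoprolol or atenolol)*.

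**Cost.** Protocol wording only, plus slightly more expedited SAE reports. No change to sample size, visits or data collected.

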## **9. Ethical and Regulatory Aspects**

### **9.1 Responsibilities of the Investigator**

The Investigator is responsible for the conduct of the trial at his/her site. He/she will ensure that the trial is performed in accordance with the Declaration of Helsinki, as well as with the ICH Note for Guidance on Good Clinical Practice (ICH E6, 1996) and applicable regulatory requirements. In particular, the Investigator must ensure that only subjects who have given their informed consent are included into the trial.

